### The AIRE study design

The design of the AIRE operational research study will incorporate data from several cross-sectional studies and one prospective interventional cohort study with short-term 14-day follow-up for the severe cases. The recruitment and collection of mixed quantitative and qualitative data will be carried out over a period of 22 months from March 2021 to November 2022 in the four countries. The collection of individual IMCI data on children carried out over a period of 12 months (June 2021 to June 2022) will allow to consider any effect of seasonality for pneumonia, malaria and malnutrition.

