**Fig. 4 Fig4:**
[figure not shown]
Inclusion process of children and follow-up in the AIRE research sites. Burkina Faso, Guinea, Mali, Niger, June 2021–June 2022

All the neonates (0 to 59 days) and children (2 to 59 months) attending IMCI consultation in the research sites of the AIRE project will be screened by the HCW in place at the PHC. They will be classified as “red case”, “yellow case” or “green case”, according to routine IMCI guidelines based on their age category.

PO will be introduced after IMCI classification for all children based on age and danger signs, except for those aged 2–59 months and classified as non-respiratory “green case”. Children could be then reclassified as severe cases using PO if SpO2 < 90% defining hypoxemia, as shown in Fig. 4 (red arrow).

Eligible children for whom at least one caregiver gives signed informed consent will be enrolled consecutively during the recruitment period, from 2021, 14th June to 2022, 20th June.

All individuals identified as severe cases (respiratory and non-respiratory) under IMCI guidelines only or using PO should be referred to the hospital: these children will be included in a short-term follow-up study until Day-14 after the index IMCI consultation, regardless of their subsequent hospitalization or not, to document their health outcomes. Data on referral to hospital, and hospitalization of the child, if applicable, will be collected. In the event of hospitalization, care for children with serious respiratory or non-respiratory diseases (oxygen therapy and antibiotic therapy, etc.) will be provided under local conditions with the support of the AIRE project. At Day-14, study team will call or visit the caregivers at home to collect data on the child health status and care pathway through Day-14. Non-severe cases identified at the PHC will return home after the IMCI consultation without further follow-up.

Follow-up supervision, training and data quality control will be provided by the clinical supervisor at operational sites, and clinical research monitors and research assistants at research sites.

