#### Outcomes evaluation

Cross-sectional study of pathways and patterns of care will be conducted among all IMCI children eligible for PO use with caregiver consent by research PHC. Children will be recruited consecutively during the 12-month.

Direct and indirect costs will be collected for a representative sub-sample of two categories of children: IMCI outpatients (green and yellow cases) and severe cases requiring hospital transfer (5 per category per PHC per month, i.e. 1920 children in total).

Day-14 health outcome will be collected only for severe cases. To assess the child mortality on Day-14 of all severe cases identified with an accuracy of plus or minus 3% per country and adding 10% lost to follow-up, we aimed to recruit at least 710 severe cases aged 2 to 23 months (mortality estimated at 10%) and 375 children aged between 24 and 59 months (mortality estimated at 5%), i.e. 1085 children between 2 and 59 months old per country over 12 months, for a total of 4340 children. We will only describe mortality in neonates (aged less than 59 days) enrolling them all over the 12 months of the operational study with a maximum of 400 per country. Overall, we will follow a maximum of 1485 children per country, i.e. a maximum of 5940 severe cases over the study period, representing approximately 15% of the total IMCI population which will be a total of 40,000 children expected for the four countries.

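### The per-country maximum on Day-14 follow-up is not reconciled with following all severe cases; applied as a stop, it would lose a country's latest months of Day-14 outcomes

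*Protocol article*

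**What the plan says.** The protocol article, Sample size, Outcomes evaluation, builds the number followed in three steps.

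- Ages 2-59 months: a lower bound per country, "we aimed to recruit at least 710 severe cases aged 2 to 23 months (mortality estimated at 10"%), together with "375 children aged between 24 and 59 months (mortality estimated at 5"%), giving 1,085.
- Ages 0-59 days: mortality is only described, "enrolling them all over the 12 months of the operational study with a maximum of 400 per country".
- Total: "we will follow a maximum of 1485 children per country, i.e. a maximum of 5940 severe cases over the study period", described as "representing approximately 15% of the total IMCI population which will be a total of 40,000 children expected for the four countries".

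Elsewhere there is no maximum. The section on study population and patient inclusion says that eligible children with consent "will be enrolled consecutively during the recruitment period", which runs from 14 June 2021 to 20 June 2022, and places every severe case in the Day-14 study. Individual data collection and End of search both have all severe cases followed to Day 14. Descriptive analysis reports the Day-14 outcome for all severe cases identified at the health centers. The AIRE study design section justifies 12 months of individual data because they "will allow to consider any effect of seasonality for pneumonia, malaria and malnutrition".

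**The concern.** The sample-size section and the other four sections describe different follow-up populations, one bounded and one complete. The bounded one is also inconsistent internally, since a minimum for ages 2-59 months is added to a maximum for younger infants and the sum is called a maximum. In a country with 400 young infants, the room left for older children is 1,485 - 400 = 1,085, so floor and ceiling coincide.

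The order of recruitment is what makes this matter. If a field team read the maximum as a stop, consecutive recruitment means that the children not followed would be the last to arrive. Day-14 mortality in that country would then describe the earlier part of the year, although a full year was chosen because pneumonia, malaria and malnutrition vary by season. The reasons for missed referral would be cut in the same way, because Table 2 schedules them only at the Day-14 contact.

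**Working it through.** **Inputs from Sample size, Outcomes evaluation:** 710, 375, 400, 1,485, 5,940, 40,000 and approximately 15%. **Assumptions, not in the document:** even accrual over 12 months, equal country shares unless stated, every severe rate other than 15%, and the maximum acting as a hard stop.

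**1. The plan's own figures reproduce.** 710 + 375 = 1,085; 1,085 × 4 = 4,340; 1,085 + 400 = 1,485; 1,485 × 4 = 5,940; 5,940 / 40,000 = 14.85%, stated as approximately 15%.

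The 15% is therefore the maximum divided by the expected population. It is not an independent estimate of how many children will be severe, so it cannot show whether the maximum is tight or generous.

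**2. When a hard stop would bind, equal countries.** Month reached = 12 × 5,940 / expected severe cases. Share lost = 1 - 5,940 / expected severe cases.

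| Severe among 40,000 | Expected cases | Month reached | Share not followed |
|---|---|---|---|
| 10% | 4,000 | never | 0 |
| 12% | 4,800 | never | 0 |
| 15% | 6,000 | 11.9 | 1% (60 cases) |
| 17.5% | 7,000 | 10.2 | 15% |
| 20% | 8,000 | 8.9 | 26% |
| 25% | 10,000 | 7.1 | 41% |

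**3. Unequal countries at a total of 6,000.** The same 1,485 applies to every country, and the section gives no country split of the 40,000. Month reached = 12 × 1,485 / (share × 6,000).

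- 25% share: 1,500 cases, month 11.9
- 30% share: 1,800 cases, month 9.9
- 40% share: 2,400 cases, month 7.4

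So the maximum can bind early in one country without any excess overall.

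**4. Infants aged 0-59 days.** Month reached = 12 × 400 / expected. It is not reached at 400 or fewer, and is reached at month 9.6 with 500 and month 8.0 with 600.

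**5. Which data would be cut.** Classification and the referral decision are recorded at Day 0 for all eligible consenting children. Hospital data are collected on all patients referred from the research centers, by a data collector at each district hospital. Neither carries a maximum. Vital status at Day 14 and the reasons for missed referral come from the Day-14 contact, and these would be lost.

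**The case against.** The strongest reply is that nothing in the article closes follow-up early. Enrolment ends on a calendar date, the research ends with the Day-14 follow-up of the last child included, and the sentence on young infants itself speaks of the whole 12 months. A total built on a lower bound reads naturally as a workload estimate, and an article may leave its operation to the full protocol. All of this stands as an argument about intent. It does not remove the contradiction, because the sentence "we will follow a maximum of 1485 children per country" limits follow-up in plain terms and the other sections do not.

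A reader might go further in four ways that the document does not support.

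- That Day-14 ascertainment does stop at the maximum. No passage says so.
- That the maximum has no margin, because 15% of 10,000 children per country is 1,500 against 1,485. That comparison is circular: the 15% is 5,940 / 40,000 rounded, and the gap of 15 is the rounding.
- That seasonality cannot be estimated for severe cases. The analysis section names seasonality for being a severe case, being hospitalized and non-referral, not for the Day-14 mortality model. Day-0 and hospital data have no maximum.
- That season and country would become confounded. A country cut at month 8 still shares eight months with the others, so both effects remain estimable, with less information on the late months.

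**Conclusion.** The concern holds as an unreconciled contradiction with a conditional consequence. The article sets a maximum on Day-14 follow-up beside a lower bound and beside complete follow-up, and does not say which governs. If the maximum is used as a stop, a country exceeding it loses its latest months of Day-14 vital status and reasons for missed referral, and its Day-14 mortality does not cover the full year.

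Whether this would happen cannot be settled from the document. Under the assumptions above, the effect runs from none (10-12% severe), through about 1% of cases at 15%, to 41% at 25%. A single country with 30% or 40% of 6,000 cases would be cut at month 9.9 or 7.4 even at that overall total. The point deserves correction because the wording is easily fixed and the loss would fall by calendar time rather than at random.

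**What to change.** In Sample size, Outcomes evaluation, state that 1,485 and 400 per country are planning figures and that all severe cases are followed to Day 14 throughout the recruitment period. This agrees with the sections on study population, individual data collection and end of search. The cost is some additional Day-14 calls or visits in busy countries.

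If workload requires a real cap, apply it as a monthly quota per research center, with weights equal to the inverse of the fraction followed in each center and month. The same section already does this for the cost sub-sample, with 5 children per category per center per month. Spread evenly over 4 centers and 12 months, 1,485 comes to 1,485 / 48 = 30.9 children per center per month. Because large and smaller centers were chosen on purpose, the quota could be set in proportion to size. The denominators for the weights come from the Day-0 data, so the cost is a simple weighted analysis.

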### Data analysis

#### Context evaluation

We will carry out a baseline description of the infrastructure of the PHC: number and % of PHC having access to electricity or the Internet, average distance between the PHC and the DH, a map of all the health facilities). Furthermore, we will conduct a description of the functioning of PHC and HCW: number and % of PHC using electronic compared to paper-based IMCI, hospital transfer capacities and modalities, health services, qualification of HCW and average number of HCW per PHC.

We will describe the functioning of the PHC and staff turnover over the study period: in % compared to baseline. The epidemiological characteristics of IMCI consultations will be described stratified by country and disaggregated by age (0–59 days, 2–59 months) and sex (male, female), mean monthly number of IMCI consultations and standard deviation, with % of PO uptake, mean monthly number and prevalence of severe cases globally and according to the type of IMCI (paper or electronic), and after the use of PO, their type (respiratory or not) identified with indication of hospital referral, coverage in % of decided hospital transfer among the severe cases identified.

#### Process evaluation

##### Acceptability

Quantitative acceptability data will be analyzed using descriptive and inferential statistics. Regression models will help understand the individual and contextual determinants of acceptability. An analysis of the difference in acceptability before and after the implementation of the PO as well as after the end of the project will make it possible to measure the effects of the implementation of the project on the prospective, concurrent and retrospective acceptability. Qualitative data will be analyzed using an analytical framework analysis approach [56] to compare the empirical data with the theoretical model used for data collection through Nvivo software.

##### Implementation fidelity

The data will be analyzed according to the method of the analytical framework [56] using the framework adapted from Carroll et al. [48]. Qualitative data on the fidelity of activity content will be converted into quantitative data by considering the proportions of activities ranked by respondents as 1) implemented as planned; 2) not implemented; 3) planned but modified; and 4) added. A fifth option, “non-response” will be added to account for missing responses. Temporal fidelity will be examined in terms of frequency (eg monthly, quarterly) and if possible duration, understood as the number of days planned for this activity. The results will be presented graphically for each district and country.

##### Process and realist evaluation

The qualitative data will be fully transcribed and then integrated into the NVivo software to analyze the data and compare them with the theoretical model of Greenhalgh et al. [52]. For the realist evaluation and development of the final Mid-Range-Theory, an abductive approach will be used to identify the Context – Mechanisms – Outcome configurations from the existing theories in the literature and from all the data collected in the project, in order to highlight the contexts in which the mechanisms are (or are not) triggered, and the resulting outcomes. This approach aims to construct a theoretical explanation of a phenomenon. This dialogue between theoretical literature and empirical data will allow us to build and gradually refine the Mid-Range-Theory. The semi-regularities will be identified in the data collected by the content analysis of the NVivo software and then modeled in a process-oriented way. More specifically, we will take up the four steps proposed by Abimbola et al. [57] to: 1) identify the effects; 2) identify the contextual components related to the effects; 3) theoretically reconstruct the links between the context and the effects; 4) identify the mechanisms.

#### Outcome evaluation

##### Descriptive analysis

The analysis will first describe and analyze each of the following results stratified by country:Characteristics of children under 5, eligible for PO during IMCI consultation: distribution by age, sex, distance from home to PHC, socio-demographic variables, rural/urban PHC, clinic IMCI classification, type of case (respiratory or not), PO uptake (%), SpO2 level measurement (mean and % of hypoxemia [severe< 90% and moderate 90 to 93%]) and IMCI+PO classification, IMCI management (on paper/electronic), severe cases (respiratory and non-respiratory) and rate among severe cases with hospital transfer indicated.Pathways of care (in %) stratified according to severity (IMCI+PO) and hypoxemia: history of recent attendance at PHC, duration since the onset of symptoms, effective rate of hospitalization among severe cases (proportion of hospitalizations carried out among all those identified at PHC with a hospital transfer indication, missed referral opportunities among severe cases with indication for hospital referral and reasons for non-transfer, return to PHC care, or rehospitalizations.Patterns of care for IMCI outpatients stratified according to severity (IMCI+PO) and hypoxemia, and for inpatients, hospitalization patterns: coverage of oxygen therapy, antibiotics, ACTs, and other specific treatments in %, volumes, mean time between the medical treatment and onset of symptoms, and the diagnosis of hypoxemia and mean durations of resources utilization.Costs expressed as medians with interquartile ranges, according to the severity of the case, hypoxemia, and the hospitalization by countryShort-term health outcome (deceased, alive and still treated, alive and cured, lost to follow-up) on Day-14 (in %) for all severe cases identified at the PHC level.

Descriptive statistics will include proportions for categories (with their 95% confidence intervals) and means (standard deviation) or medians (interquartile range [IQR]) for continuous variables. Differences in proportions will be tested by the Chi-square test (or Fisher’s exact test in the case of small sample sizes), and continuous variables will be compared using the t-test or Wilcoxon rank-sum test, as applicable.

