## Methods of the AIRE research protocol

### The AIRE study sites

The AIRE operational research study will be conducted in four AIRE countries where there is a high severe disease incidence: Burkina Faso, Guinea, Mali, Niger. The project will take place in two health districts per country, in a total of 8 district hospitals and 202 PHC (Fig. 3). All PHC will be considered as operational sites (from which aggregate health data will be collected) and 16 research sites will be selected among them (4 sites per country providing also individual health data). Data on the quantitative acceptability of HCW will be collected in both operational and research sites.

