##### Analysis of associated factors to the main criteria

Factors associated with being a severe case (using paper or e-IMCI and using PO or not) among IMCI outpatients, being hospitalized among severe cases, non-referral among severe cases will be studied using a multivariate logistic regression, adjusting for clustered variables (PHC, support of IMCI paper or electronic, rural/urban location), and for individual data (age, sex, socio-demographics, IMCI classification illness, comorbidities, seasonality, distance from home to PHC or district hospital, SpO2 level threshold using PO,...), using robust standard error to take into account the cluster effect within each PHC. All *P* values will be two-sided, with P values < 0.05 considered statistically significant.Kaplan-Meier estimates of the cumulative probability of oxygen therapy delivery and Day-14 survival will be performed for all identified severe cases with hypoxemia, whether hospitalized or not. Day-14 mortality associated factors will be analyzed using logistic regression. Additionally, in a sensitivity analysis missing data will be handled by using a complete data analysis and will consider the maximum bias hypothesis replacing missing data or dropouts by death values.The pathways (hospital transfer) and patterns of care (access to oxygen therapy, volume, duration) will be analyzed and their correlates investigated using a logistic regression.

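### Country-level intervals and tests of PHC-level factors make no stated allowance for clustering in 16 PHCs, and the clustered standard error is attached to only some of the logistic models

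*Protocol article*

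**What the plan says.** Under The AIRE study sites, individual data come from a small number of centres: "16 research sites will be selected among them (4 sites per country providing also individual health data").

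Under Data analysis, Outcome evaluation, Descriptive analysis, results are organised by country: "The analysis will first describe and analyze each of the following results stratified by country". The section then states "Descriptive statistics will include proportions for categories (with their 95% confidence intervals"). It gives the tests as "Differences in proportions will be tested by the Chi-square test" (Fisher's exact test for small samples), and says "continuous variables will be compared using the t-test or Wilcoxon rank-sum test, as applicable". Clustering by PHC is not mentioned, and no interval formula is given.

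The next section, Analysis of associated factors to the main criteria, covers being a severe case, being hospitalised and non-referral. It plans multivariable logistic regression "adjusting for clustered variables (PHC, support of IMCI paper or electronic, rural/urban location"), and "using robust standard error to take into account the cluster effect within each PHC". Later in that section: "Day-14 mortality associated factors will be analyzed using logistic regression". Pathways and patterns of care are likewise assigned a logistic regression. Neither of these later statements repeats the clustered standard error. Costs are compared with a mixed linear model whose random-effect level is not given.

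**The concern.** The four named tests, in their ordinary form, treat every child as an independent observation. Children seen at one PHC share staff, catchment, referral options and IMCI format, so their outcomes are likely to be correlated. The article accepts this in its regression section but not in the descriptive section just before it.

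This matters for questions the study sets itself. The objectives promise to explore electronic against paper IMCI in every component, and the Discussion repeats that comparison. IMCI format is constant within a PHC, as are country and rural or urban location. For such factors the effective sample size is governed mainly by the number of PHCs. An ordinary chi-square test read against the two-sided 0.05 rule could then turn ordinary variation between PHCs into a finding, in a study meant to inform national scale-up. In the same way, each country's Day-14 mortality, planned to within 3 points, rests on four PHCs.

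**Working it through.** **Inputs from the article.** 16 research PHCs, four per country. Table 1, with the location of electronic IMCI, gives 6 electronic PHCs (four in Burkina Faso, two in Markala) and 10 paper PHCs. Targets per country are 710 severe cases aged 2-23 months (mortality 10%) and 375 aged 24-59 months (mortality 5%), with 10% lost. The total is 4,340 severe cases aged 2-59 months, so 4,340/16 ≈ 271 per PHC. 40,000 IMCI children give 40,000/16 = 2,500 per PHC.

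**Assumption.** No ICC is given, so 0.005 to 0.05 is used throughout.

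**The plan's own sample size.** With n = 1.96² × p(1−p)/0.03², p = 0.10 gives 384, and 384/0.9 ≈ 427, against the stated 710. For p = 0.05 the result is about 226, against 375. Both stated figures are larger by a factor of about 1.66. If that factor were an unstated design effect, it would cover an ICC of only about 0.66/158.75 ≈ 0.004 at 2-23 months and 0.66/83.4 ≈ 0.008 at 24-59 months. It would not change how the intervals and tests are computed.

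**Country-level interval for Day-14 mortality.** The design effect is DE = 1 + (m − 1) × ICC, with m evaluable children per PHC.

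- 2-23 months: 710 × 0.9 = 639 evaluable, m ≈ 160. Independence half-width: 1.96 × √(0.10 × 0.90/639) = 2.3 points. DE runs from 1.79 to 8.94, so the half-width becomes 2.33 × √1.79 ≈ 3.1 to 2.33 × √8.94 ≈ 7.0 points. An independence 95% interval would cover about 86% down to 49%. With a t reference on 3 degrees of freedom (four PHCs) the half-width is 5.1 to 11.3 points.
- 24-59 months: 337.5 evaluable, m ≈ 84. The half-width of 2.3 points becomes 2.8 to 5.3, and coverage is about 90% down to 61%.

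**Chi-square test of a PHC-level factor with no true difference.** The approximate rejection rate is 2Φ(−1.96/√DE).

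| Children per PHC | ICC | DE | Formula | Simulation, 6 v 10 PHCs |
|---|---|---|---|---|
| 271 | 0.005 | 2.35 | 20% | 20% |
| 271 | 0.02 | 6.4 | 44% | 44% |
| 271 | 0.05 | 14.5 | 61% | 61% |
| 2,500 | 0.005 | 13.5 | 59% | 60% |
| 2,500 | 0.02 | 51.0 | 78% | 78% |
| 2,500 | 0.05 | 126 | 86% | 86% |

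The simulation was beta-binomial with 20,000 replicates, equal PHC sizes, and event rates of 8.3% (271 per PHC) and 15% (2,500 per PHC).

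**Chi-square test of a child-level factor balanced within PHCs.** The same simulations give 4.4-5.1%, so there is no inflation.

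**Cluster-robust Wald test of a PHC-level factor, 16 PHCs.** With an uncorrected normal reference the error is about 9-11% (12-14% if PHC sizes vary with a coefficient of variation of 0.6). With a G/(G−1) factor and t on 14 degrees of freedom it is about 6-7% (8-10% with unequal sizes).

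**The case against.** The best defence is that much of this is inferred from silence in a condensed article. The descriptive section stratifies by country and then mostly by severity, hypoxemia and hospitalisation, which are child-level attributes. It specifies no test between countries or between IMCI formats. For severe-case status, IMCI format also enters a regression that does have robust errors. The Day-14 and pathway sentences sit in the same section as the robust-error statement, and hospital transfer overlaps with outcomes that statement already covers. The cost comparison uses a mixed model, and PHC is itself listed as an adjustment variable.

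Several of these points stand, and they rule out stronger readings that a reader might infer:

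- That clustering is ignored outside one set of models: the mixed cost model and the adjustment for PHC contradict this.
- That every test and interval is too optimistic: factors balanced within PHCs are not materially affected, and the interval formula is not stated.
- That the robust standard error fails because there are few clusters: no small-sample correction is stated or excluded, an article may leave that to the analysis plan, and with 16 PHCs the inflation is modest. An error near 30% arises only with 2 v 2 PHCs, a within-country regression that the article does not specify.

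What the defence does not answer is that the tests are named, and their ordinary form assumes independence. The objectives promise the format comparison in each component. Attaching the clustered error to some models and not restating it for others leaves the Day-14 model, a main outcome analysis, open to being run unclustered. Adjusting for PHC in other models does not correct the descriptive section. If PHC enters as indicators, format and location cannot be estimated at all, which is a separate matter.

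**Conclusion.** The concern holds in a limited form. Followed as written, the descriptive section overstates certainty for factors that vary between PHCs. It does the same for country-level proportions if their intervals assume independence. The clustered standard error is not clearly extended to the Day-14 mortality, pathway and pattern models.

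The size depends on an ICC that the documents do not supply. The direction does not: even at 0.005, a chi-square test of IMCI format has about four times its nominal error with 271 severe cases per PHC. The small number of clusters behind the robust standard error is a secondary caution.

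**What to change.** 1. In Descriptive analysis, state that 95% intervals for country-level proportions allow for clustering by PHC (for example Rao-Scott or cluster-robust), and that any factor varying between PHCs (IMCI format, rural or urban location, country) is compared with a clustered test. Ordinary tests may stay for child-level factors balanced within PHCs.
2. In Analysis of associated factors, state that the PHC-clustered standard error also applies to the Day-14 mortality, pathway and pattern models.
3. As a secondary point, name a small-sample correction for the robust standard error, such as CR2 or a t reference, because there are only 16 clusters.

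This costs a few lines of text and code and needs no new data. Intervals will be wider, particularly by country with four PHCs each, and fewer results will reach significance.
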